## Abstract

**Background:**

Endoscopic resection is widely accepted as a local treatment for rectal neuroendocrine tumors sized ≤ 10 mm. However, there is no consensus on the best method for the endoscopic resection of rectal neuroendocrine tumors. As a simplified endoscopic procedure, endoscopic submucosal resection with a ligation device (ESMR-L) indicates a histologically complete resection rate comparable to that of endoscopic submucosal dissection (ESD). We hypothesized that ESMR-L than ESD would be preferred for rectal neuroendocrine tumors. Hence, this trial aimed to verify whether ESMR-L is non-inferior to ESD in terms of histologically complete resection rate.

**Methods:**

This is a prospective, open-label, multicenter, non-inferiority, randomized controlled trial of two parallel groups, conducted at the Shizuoka Cancer Center and 31 other institutions in Japan. Patients with a lesion endoscopically diagnosed as a rectal neuroendocrine tumor ≤ 10 mm are eligible for inclusion. A total of 266 patients will be recruited and randomized to undergo either ESD or ESMR-L. The primary endpoint is the rate of en bloc resection with histologically tumor-free margins (R0 resection). Secondary endpoints include en bloc resection rate, procedure time, adverse events, hospitalization days, total devices and agents cost, adverse event rate between groups with and without resection site closure, outcomes between expert and non-expert endoscopists, and factors associated with R0 resection failure. The sample size is determined based on the assumption that the R0 resection rate will be 95.2% in the ESD group and 95.3% in the ESMR-L group, with a non-inferiority margin of 8%. With a one-sided significance level of 0.05 and a power of 80%, 226 participants are required. Assuming a dropout rate of 15%, 266 patients will be included in this study.

**Discussion:**

This is the first multicenter randomized controlled trial comparing ESD and ESMR-L for the R0 resection of rectal neuroendocrine tumors ≤ 10 mm. This will provide valuable information for standardizing endoscopic resection methods for rectal neuroendocrine tumors.

**Trial registration:**

Japan Registry of Clinical Trials, jRCTs042210124. Registered on Jan 6, 2022.

## Background

Neuroendocrine tumors (NETs) are rare, however, their incidence and prevalence are increasing globally [1]. The gastrointestinal tract is the leading primary site of NETs, particularly rectal NETs, which commonly occur among Asian/Pacific Islanders [1–3]. Considering the increasing prevalence of rectal NETs, effective management strategies are crucial in clinical practice. The management of rectal NETs depends on the tumor size and depth. NETs measuring ≥ 20 mm or showing invasion of the muscularis propria (MP) require radical surgery because of their high metastatic potential. The management of lesions sized 10–20 mm is debatable in the guidelines; however, this size category has been associated with a significant lymph node metastasis rate of 30–66% [3, 4]. In contrast, for rectal NETs measuring ≤ 10 mm, the rate of lymph node metastasis was 3%, and the 5-year cancer-specific survival rate was 100% in patients undergoing both local excision and radical surgery [5]. It is widely accepted that lesions sized ≤ 10 mm without MP invasion are suitable for local resection, with endoscopic resection being recommended in several guidelines due to its minimal invasion [6–8]. Reports indicate various methods for the endoscopic resection of rectal NETs, including polypectomy, conventional endoscopic mucosal resection (EMR), endoscopic submucosal dissection (ESD), modified EMR, such as cap-assisted EMR (EMR-C), and endoscopic submucosal resection with a ligation device (ESMR-L) [9–30]. The primary objective of the endoscopic resection of NETs is to achieve histologically complete resection (R0 resection) [8]. Previous meta-analyses have compared different techniques, such as modified EMR and ESD, with conventional EMR. However, it revealed varying results regarding the superiority of one method over the other in terms of R0 resection rates. One meta-analysis demonstrated the superiority of modified EMR to ESD (R0 rates:93.7% vs. 84.1%), whereas another reported no significant differences (94.4% vs. 91.8%) [31, 32]. However, these meta-analyses were based on retrospective studies and no multicenter randomized controlled trials (RCT) have directly compared these techniques. Therefore, the current evidence level remains low, as stated in the recent European Society of Gastrointestinal Endoscopy (ESGE) guideline [8]. Consequently, there is no consensus on the optimal method for endoscopic resection of rectal NETs. ESD is considered the most reliable resection technique for colorectal adenomas and superficial cancers, with a high R0 resection rate [33, 34]. However, ESD is associated with longer procedure times and requires expensive specialized equipment, whereas modified EMR is a simpler and less technically demanding approach [32]. Among the modified EMR, ESMR-L has shown a relatively higher R0 resection rate (89–100%) than EMR-C (83–92%) [30–32]. Given these considerations, if ESMR-L achieves R0 resection rates comparable with those of ESD, it may be preferred for rectal NETs.

The BANDIT trial aims to verify whether ESMR-L is inferior to ESD in terms of the R0 resection rate.

## Methods and design

### Study settings

This is a prospective, open-label, multicenter, non-inferiority RCT of two parallel groups, conducted at the Shizuoka Cancer Center and 31 other institutions in Japan. A flowchart of the BANDIT trial is displayed in Fig. 1. The trial protocol was designed according to the Standard Protocol Items: Recommendations for Interventional Trials (SPIRIT) guidelines [35]. The SPIRIT flow diagram is shown in Fig. 2.

**Fig. 1 Fig1:**
[figure not shown]
Flowchart of the study design. ESD, endoscopic submucosal dissection; ESMR-L, endoscopic submucosal resection with a ligation device

**Fig. 2 Fig2:**
[figure not shown]
Schedule of enrollment, interventions, and assessments as per Standard Protocol Items: Recommendations for Interventional trials (SPIRIT). ESD, endoscopic submucosal dissection; ESMR-L, endoscopic submucosal resection with a ligation device

### Approvals

The study protocol was approved by the Certified Review Board (CRB) of Shizuoka Cancer Center (CRB4180010; Nov 24, 2021). The trial was registered in the Japan Registry of Clinical Trials (jRCTs042210124; Jan 6, 2022).

### Eligibility criteria

#### Inclusion criteria

Patients should meet all of the following criteria.1) Patients with a lesion endoscopically diagnosed as rectal NET ≤ 10 mm.2) Patients who are at least 20 years old at the time of obtaining consent.3) Written informed consent should be provided based on the free will of patients after they have thoroughly understood the instructions provided regarding study participation.

#### Exclusion criteria

Patients are excluded if they met any of the following criteria.1) Patients whose clinical course cannot be followed up to 28 days after treatment.2) Patients with a recurrent lesion.3) Patients with inflammatory bowel disease or colorectal polyposis.4) Patients with coagulation dysfunctions.5) Patients with severe infectious disease.6) Patients on dialysis.7) Patients who cannot discontinue antithrombotic agents based on the guidelines for gastroenterological endoscopy in patients undergoing antithrombotic treatment [36, 37].8) Pregnant patients.9) Other cases determined to be unfit for the study by the investigator.

### Informed consent procedure

Patients are screened for eligibility by endoscopists at each institution based on the above-mentioned criteria. The patients will receive detailed information about the trial from a member of the research team at their respective institutions. Ample time will be provided to patients for considering participation in the trial. Written informed consent will be obtained from each patient before enrollment.

### Randomization

Upon enrollment of eligible patients by the investigators, a randomization process will be conducted to assign patients to either the ESD or the ESMR-L group. This randomization will follow a 1:1 allocation ratio and will be performed using a web-based registration system available at Shizuoka Cancer Center, which is accessible 24 h a day. This study will use minimization method. Adjustment factors are participating institutions and endoscopist expertise levels (expert or non-expert).

### Blinding

Owing to the nature of the trial intervention, blinding endoscopists, and patients is not feasible. Endoscopists should be aware of the allocated group at the time of treatment, and patients may become aware of their assigned group during the course of treatment.

### Trial interventions

Each patient with a rectal NET is treated using the assigned endoscopic procedure. Only one target lesion is treated per patient. Hospitalization is recommended, however, it is not mandatory.

### Standard treatment group (ESD group)

ESD is a procedure involving a mucosal incision and submucosal dissection using ESD knives [38]. ESD knives are specified to the following; DualKnife J (KD-655, Olympus Medical Systems Corp, Tokyo, Japan), FlushKnife BT-S (DK2620J, Fujifilm, Tokyo, Japan), HookKnife J (KD-625, Olympus Medical Systems Corp), and Jet B-knife (Zeon Medical Inc, Tokyo, Japan). The endoscope is selected at the discretion of the operator. CO2 insufflation is recommended. This trial does not specify the type and mode of the electrosurgical unit, the use of a distal attachment, or the type of solution for submucosal injection. Traction devices are allowed to use. In cases of intraprocedural bleeding, hemostasis is achieved through coagulation with the tip of the ESD knife or hemostatic forceps. If intraprocedural perforation or muscle injury occurs, the resection site will be clipped.

### Trial treatment group (ESMR-L group)

ESMR-L will be performed using an endoscope equipped with a band ligator device (Pneumoactivate EVL device, SB-Kawasumi Laboratories, Inc, Tokyo, Japan) [9]. The lesion will be removed using submucosal injection. Subsequently, the lesion will be aspirated into the ligator device, followed by the deployment of the elastic band. Afterward, snare resection will be performed below the band using a blended current. The endoscope is selected at the discretion of the operator. CO2 insufflation is recommended. The type of solution used for the submucosal injection and the type of snare employed are not specified. In cases of bleeding immediately after resection, hemostasis is achieved by coagulation with the tip of the snare, hemostatic forceps, or clipping. If intraprocedural perforation or muscle injury occurs, the resection site will be clipped.

### Intervention success and failure

Treatment is considered successful when the operator determines that the specimen has been retrieved without any residual lesions. In cases where the operator deems it impossible to complete the resection using the assigned treatment and specified devices, the treatment protocol will be terminated. Additional treatment options may be allowed after termination.

### Restrictions after resection

In the absence of perforation or muscle injury, prophylactic clipping or covering methods, such as polyglycolic acid sheets and fibrin glue, are not recommended, however, they are permitted. If the operator applies prophylactic clipping or covering methods, they are required to apply the same method to both the ESD and ESMR-L groups. Prophylactic endoscopic coagulation is permitted only for visible vessels.

### Pathological assessment

Resected specimens are immediately fixed on a panel using pins in a manner that aligns with the tumor diameter. To evaluate the maximum cut surface and vertical margins, the specimens are fixed in 10% buffered formalin and sectioned at the deepest part of the tumor. Resected specimen size, tumor size, classification (NET G1, G2, G3, neuroendocrine carcinoma [NEC]), invasion depth, lymphatic invasion, vascular invasion, horizontal margins, and vertical margins are recorded. Final pathological diagnoses will be determined by pathologists at each participating institution utilizing the WHO Classification of Tumors, 5th Edition (2019) and the Japanese Classification of Colorectal Carcinoma [39].

Additional colectomy with lymphadenectomy may be considered for the following; tumor size ≥ 1 cm or grade higher than G2, positive vertical margins, muscularis propria invasion, or lymphovascular invasion [40].

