### Outcome measures

#### The primary endpoint (for non-inferiority)

1. Rate of en bloc resection with histologically tumor-free margins (R0 resection rate)

R0 resection rate is defined as the absence of tumor involvement in both the horizontal and vertical margins, as confirmed histologically in the resected specimen. Evaluation of the horizontal and vertical margins should be performed on the plane where the NET or NEC is present. Margins without NET or NEC, irrespective of the distance, are considered to be tumor-free. Subsequently, R0 resection will be assessed by the operator based on a pathological report.

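### The plan states no masking of the pathologists who read the margins, and the unmasked operator then assigns R0, the primary endpoint

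*Protocol article*

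**What the plan says.** All references are to the Protocol article.

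- **Study settings:** "This is a prospective, open-label, multicenter, non-inferiority RCT of two parallel groups".
- **Blinding:** "Owing to the nature of the trial intervention, blinding endoscopists, and patients is not feasible". The section adds that "Endoscopists should be aware of the allocated group at the time of treatment". It does not mention pathologists.
- **Pathological assessment:** horizontal and vertical margins are among the recorded items, and "Final pathological diagnoses will be determined by pathologists at each participating institution". No central reading, second reading or masked reading is described.
- **The primary endpoint:** "R0 resection rate is defined as the absence of tumor involvement in both the horizontal and vertical margins", confirmed on histology. The section adds "Margins without NET or NEC, irrespective of the distance, are considered to be tumor-free". It closes by stating that "R0 resection will be assessed by the operator based on a pathological report".

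**The concern.** The reason given for not masking, the nature of the intervention, applies to the people who perform or undergo the procedure. It does not carry over to someone reading a slide. Yet the two people who produce the primary endpoint are the local pathologist, for whom no masking is stated, and the operator, who is stated to know the arm. No stated safeguard separates the allocation from the outcome.

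In a non-inferiority trial, lenient reading of ESMR-L margins or strict reading of ESD margins pushes the result towards the claim. The opposite tendency costs power and could lose a true claim. Failures are expected to be few, so the result is sensitive to a small number of readings.

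**Working it through.** **Inputs (Sample size calculation; Statistical analyses).** R0 95.2% for ESD and 95.3% for ESMR-L; margin 8 percentage points; one-sided alpha 0.05; power 80%; 226 evaluable (113 per arm); 15% dropout; 266 enrolled; Farrington–Manning test.

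**1. The plan's own figure.** Per-arm size is n = [(z₀.₉₅·s₀ + z₀.₈₀·s₁) / (0.08 + p_T − p_C)]², where s₀ uses the rates fitted under the null (difference fixed at −0.08) and s₁ uses the assumed rates.
- Rates as stated: s₀ = 0.3554, s₁ = 0.3008, so n = [(1.645 × 0.3554 + 0.842 × 0.3008) / 0.081]² = 107 per arm, 214 in total.
- Rates swapped between arms: s₀ = 0.3544, denominator 0.079, n = 112.006, so 113 per arm, 226 in total.
- Dropout: 226 / 0.85 = 265.9, rounded up to 266.

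The planned size is therefore reproduced under a standard variant and is slightly conservative for the rates as stated. Masking the reader changes none of these figures.

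**2. Expected failures at 113 per arm.** ESD: 113 × 0.048 = 5.4. ESMR-L: 113 × 0.047 = 5.3.

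**3. Where the decision turns.** The test statistic is (p̂_T − p̂_C + 0.08) / SE₀, to be compared with 1.645. With 5 ESD failures:

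| ESMR-L failures | Difference | SE₀ | Statistic | Non-inferior? |
|---|---|---|---|---|
| 5 | 0 | 0.0328 | 2.44 | yes |
| 7 | −0.0177 | 0.0335 | 1.86 | yes |
| 8 | −0.0265 | 0.0339 | 1.58 | no |

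From 5 versus 5, three further ESMR-L failures are needed to lose the claim. At 7 versus 5, one is enough.

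**4. Bias towards the claim.** Set the truth at the margin: ESD 95.2%, ESMR-L 87.2% (113 × 0.128 = 14.5 true ESMR-L failures). Let a share f of positive ESMR-L margins be read as clear, so the observed ESMR-L rate is 0.872 + 0.128f. Summing the binomial probabilities over the exact rejection region gives:

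| f (assumed) | Specimens misread (14.5 × f) | Observed ESMR-L rate | Exact false-claim rate |
|---|---|---|---|
| 0 | 0 | 87.20% | 4.7% |
| 5% | 0.7 | 87.84% | 6.7% |
| 10% | 1.4 | 88.48% | 9.2% |
| 20% | 2.9 | 89.76% | 16.8% |

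**5. Bias against the claim.** Set the truth at the planned rates and lower the ESMR-L rate by k/113:

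| Extra ESMR-L positives, k (assumed) | Exact power |
|---|---|
| 0 | 84.6% |
| 1 | 73.8% |
| 2 | 61.3% |
| 3 | 48.6% |

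Steps 4 and 5 describe different truths and should not be combined.

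**The case against.** **Silence is not evidence of unmasked reading.** A reader might infer that pathologists are told the technique. The article does not say so, and it mentions no specimen or request form. It condenses a fuller protocol that is not shown. This limits the claim about pathologists to the absence of a stated safeguard. It does not remove the point: the article has a Blinding section, a detailed pathology section and an explicit rule on who assigns R0, so the chain of outcome assessment is stated. The operator step is documented as unmasked.

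**The endpoint is partly standardised.** Specimens are pinned and cut at the deepest part of the tumor, margins are read on the plane containing tumor, and distance is irrelevant. A reader might take the any-distance rule as a source of judgement. It is in fact a binary rule that removes judgement about distance. What remains is whether tumor reaches the edge. The article says nothing about cautery damage at the margin, so nothing here rests on it.

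**The direction of bias is unknown.** Nothing shows that pathologists would favour ESMR-L over the standard technique. That stands, and it is why both directions are shown.

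**One or two readings need not decide the trial.** A reader might infer from the small counts that they would. That is true only near the boundary; from equal counts of 5 it takes three.

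**Masking may fail.** The specimen itself may reveal the technique, and the documents do not settle how often. This stands as a limit on the remedy.

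**Conclusion.** The point holds as a design weakness that should be addressed. The plan justifies the lack of masking for endoscopists and patients only, states none for the margin readers, and gives the R0 call to someone who knows the arm. It does not show that bias exists or which way it would run.

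The size depends on assumed misreading. With the truth at the margin, 5% to 20% of positive ESMR-L margins read as clear raises the false-claim rate from 4.7% to between 6.7% and 16.8%. With the truth at the planned rates, 1 to 3 extra ESMR-L positives per 113 lower power from 84.6% to between 73.8% and 48.6%. These figures assume 113 evaluable patients per arm, an ESD rate of 95.2%, and misreading confined to ESMR-L specimens. The sample size is unaffected.

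**What to change.** 1. **Blinding and Pathological assessment:** state whether margin readers know the technique. For specimens still to be read, leave the assigned technique off the trial specimen form, so that the pathologist records both margins without being told the arm.
2. **Case record:** add one field for whether the technique was apparent to the pathologist. Report it descriptively only. Do not compare R0 by this answer: it arises after randomization, is likely to be related to arm, and would split about 5 failures per arm.
3. **Primary endpoint:** replace the operator's assessment with a fixed derivation from the recorded fields. R0 is met if the horizontal margin is clear, the vertical margin is clear and the resection was en bloc. This removes the operator's discretion but cannot repair margins read with the arm known, so step 1 is still needed.

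**Cost.** No extra reader or central review is proposed. Forms change at up to 32 institutions, the data capture system gains a field and a derivation, and the review board must be notified of the protocol change. Recruitment began in June 2022, so specimens already read cannot be masked. Masking of the rest will be partial where the specimen reveals the technique.

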### Outcome measures

#### The primary endpoint (for non-inferiority)

1. Rate of en bloc resection with histologically tumor-free margins (R0 resection rate)

R0 resection rate is defined as the absence of tumor involvement in both the horizontal and vertical margins, as confirmed histologically in the resected specimen. Evaluation of the horizontal and vertical margins should be performed on the plane where the NET or NEC is present. Margins without NET or NEC, irrespective of the distance, are considered to be tumor-free. Subsequently, R0 resection will be assessed by the operator based on a pathological report.

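### The unblinded operator makes the final R0 call, and the sentence defining R0 leaves out the en bloc condition that the endpoint heading requires

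*Protocol article*

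**What the plan says.** All references are to the protocol article.

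- **Who decides.** Outcome measures, primary endpoint: "Subsequently, R0 resection will be assessed by the operator based on a pathological report".
- **What that person knows.** The Blinding section says masking of endoscopists and patients is not feasible, and adds: "Endoscopists should be aware of the allocated group at the time of treatment".
- **What the endpoint is called.** The numbered heading reads "Rate of en bloc resection with histologically tumor-free margins (R0 resection rate", and the abstract names the endpoint in the same way.
- **How it is then defined.** The sentence directly below reads: "R0 resection rate is defined as the absence of tumor involvement in both the horizontal and vertical margins, as confirmed histologically in the resected specimen". It does not mention removal in one piece.
- **The margin rule.** "Margins without NET or NEC, irrespective of the distance, are considered to be tumor-free".
- **What is captured.** Under Pathological assessment, local pathologists make the final diagnosis, and "horizontal margins, and vertical margins are recorded". En bloc resection is a separate secondary endpoint, defined as removal in one piece with no visible tumor left.

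**The concern.** Two features combine. First, the last step in classifying the only primary endpoint goes to an unblinded person judging the result of their own procedure. This is a positive instruction in the text, not a detail that a condensed article has left out. Second, the heading and the definition sentence disagree on a piecemeal specimen with free margins: it is R0 by the sentence and not R0 by the heading. As written, the operator would settle that conflict case by case.

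Failures are expected to be few, so a small number of classifications can matter to the non-inferiority decision. The discretion also serves no purpose. If the operator's call always agrees with a fixed rule, the rule loses nothing. If it differs, the difference is unblinded judgement.

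**Working it through.** **Inputs.** From Sample size calculation and Statistical analyses: R0 95.2% (ESD) and 95.3% (ESMR-L), margin 8 points, one-sided alpha 0.05, power 80%, 226 evaluable and 266 enrolled, Farrington–Manning test. 1:1 allocation gives 113 evaluable per arm. The misreading rates used below are assumptions; the documents give none.

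**The plan's own figure.** 226 / 0.85 = 265.9, so 266. An unpooled formula with continuity correction gives 220, within 3% of 226. The Farrington–Manning formula with the stated rates gives 107 per arm, 214 in total. So 226 is on the safe side, and exact power at 113 per arm is 84.6%. This point does not dispute the sample size.

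**The two definitions side by side.**

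| Specimen | Definition sentence | Heading and abstract |
|---|---|---|
| One piece, both margins free | R0 | R0 |
| One piece, a margin involved | not R0 | not R0 |
| Piecemeal, both margins free | R0 | not R0 |

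**Weight of one classification.** 1/113 = 0.88 percentage points, and 0.88/8 = 11% of the margin.

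**Expected failures, two separate scenarios.**
- Planning rates: 113 × 0.048 + 113 × 0.047 = 5.4 + 5.3 = 10.7 in the trial.
- True difference exactly at the margin (ESMR-L 87.2%, ESD 95.2%): 113 × 0.128 + 113 × 0.048 = 14.5 + 5.4 = 19.9.

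**Test statistic.** Z = (pE − pC + 0.08) / SE0, with pE and pC the observed R0 rates for ESMR-L and ESD. SE0 = √{[qE(1 − qE) + qC(1 − qC)] / 113}, where qE and qC are the maximum-likelihood rates under qE = qC − 0.08. Non-inferiority is declared if Z > 1.645.

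**Decision boundary.** With 5 ESD failures, 7 ESMR-L failures give Z = 1.86 (declared) and 8 give Z = 1.58 (not declared). With 6 ESD failures, the boundary lies between 8 (Z = 1.78) and 9 (Z = 1.51). At these points a single patient's classification changes the conclusion.

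**False non-inferiority at the margin.** The binomial probabilities of all outcome pairs with Z > 1.645 are summed at 113 per arm. An average of r ESMR-L failures read as R0 shifts the apparent rate to 0.872 + r/113. Over-calling a fraction f of failures in both arms gives 0.872 + 0.128f and 0.952 + 0.048f.

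| Assumed misreading | Apparent ESMR-L | Apparent ESD | Chance of declaring non-inferiority |
|---|---|---|---|
| None | 87.2% | 95.2% | 4.7% |
| One ESMR-L failure on average | 88.1% | 95.2% | 7.6% |
| Two ESMR-L failures on average | 89.0% | 95.2% | 11.7% |
| 10% of failures, both arms | 88.5% | 95.7% | 7.3% |
| 14% of failures, both arms | 89.0% | 95.9% | 8.7% |
| One ESD failure only | 87.2% | 96.1% | 2.8% |

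The 14% row applies to both arms the proportion implied by two ESMR-L misreadings (2/14.5).

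**The case against.** **The operator has little room.** The call rests on the pathology report, local pathologists make the diagnosis, and the article fixes both the plane of evaluation and the rule that any tumor-free distance counts. This largely stands: for a clearly negative or clearly positive report the operator only transcribes. Discretion is confined to unclear reports and piecemeal specimens, and nothing in the article shows how often these occur.

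**En bloc is part of the endpoint.** It is in the heading immediately above the definition and in the abstract, so read as a whole the section requires it. This also stands. A reader might infer that the requirement is absent from the primary endpoint, but it is missing only from one sentence. What remains is an inconsistency that needs two words to repair.

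**The direction of bias is assumed.** Operators judge their own cases in both arms, so leniency could apply to ESD as well. This stands too. Over-calling confined to ESD makes the test conservative (2.8%), and equal proportions in both arms inflate the error less than the same proportion in ESMR-L alone (8.7% against 11.7%).

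**How unassessable margins count may be settled in the full protocol.** Agreed. Their absence from the article is not part of this point; the fix covers them so that the derivation rule is complete.

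None of these arguments gives a reason to keep the operator's step or two definitions that disagree.

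**Conclusion.** The point holds as a risk that should be removed, not as a demonstrated bias. Two facts are established from the text: the final R0 call belongs to an unblinded operator, and the definition sentence conflicts with the heading and the abstract on piecemeal resection with free margins.

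The size is illustrative. Under the assumed misreadings, the one-sided error at the margin ranges from 2.8% to 11.7%, against 4.7% with none.

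Three stronger readings are tempting and are not supported:

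- *The trial is tilted towards ESMR-L.* The article sets out a preference for the simpler technique if it proves comparable, but it contains no misclassification rate and nothing that fixes a direction.
- *Only about 11 failures stand behind the inflated error rates.* The 10.7 belongs to the planning scenario. The error rates belong to the at-margin scenario, where about 20 failures are expected.
- *A derived endpoint would be objective.* En bloc status still depends on the operator's endoscopic view that no tumor remains, and the article does not say whether pathologists are masked.

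Severity: should fix. No stated figure is wrong.

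**What to change.** Replace the sentence that gives the assessment to the operator with a derivation rule, for example:

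> *R0 is derived by the data centre. A patient has R0 resection if the resection was en bloc (as defined for the secondary endpoint) and the pathologist reported both the horizontal and the vertical margin as negative. Any other value, including piecemeal removal and a margin that cannot be assessed, counts as non-R0.*

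Add en bloc to the definition sentence so that it agrees with the heading and the abstract.

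**Cost.** One derived variable and two edited sentences, with no additional reader. The margins are already recorded. En bloc status must be collected for the secondary endpoint, although the article does not list it as a data field, so this should be confirmed. The observed R0 rate may be slightly lower, because unclear cases count as failures. The sample size stays at 226 evaluable and 266 enrolled.

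**Limit.** This removes the operator's last classification step only. It does not mask the endoscopic judgement of residual tumor or the reading of the margins.
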